### Objectives

The goal of this study is to examine the effectiveness of MBRP delivered via Health Insurance Portability and Accountability Act (HIPAA)–compliant Zoom in promoting whole-person recovery from AUD, and to examine whether MBRP in this context affects mechanisms of behavior change based on the neurobiologically-informed addiction cycle domains as predictors of AUD recovery. Further, this study uses a hybrid effectiveness-implementation type 1 design [60] to prospectively test the effectiveness of MBRP, as well as identify barriers and facilitators of MBRP group participation and facilitation. Individuals (n=470) who have recently expressed interest in changing their drinking or have recently stopped or reduced drinking with or without formal treatment are randomized to receive either MBRP or referral to online mutual support using urn randomization to balance groups on patient birth sex and severity of AUD. We hypothesize that receiving MBRP, versus online mutual support, will be associated with greater odds of recovery from AUD up to 3 years following a drinking change attempt, as indicated by AUD remission, cessation of heavy drinking, and improvements in functioning and well-being. We also test whether addiction cycle domains mediate the effect of treatment on recovery, and hypothesize that MBRP will be associated with greater improvements in executive functioning and self-efficacy, and reductions in incentive salience and negative emotionality in the 3 years following a change attempt, and these constructs predict recovery outcomes. Finally, using a hybrid type 1 effectiveness-implementation design, we examine facilitators and barriers to participation and engagement in MBRP, and assess the adoption, implementation, reach, effectiveness, and maintenance of MBRP via video telehealth as continuing care in communities nationwide. This hybrid effectiveness-implementation trial is referred to herein as the Telehealth Resources for Individualized Recovery (THRIVE) goals study.

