## Methods

### Trial Design

The trial is a parallel group randomized clinical trial with individuals randomized to receive either MBRP or referral to online mutual support using urn randomization to balance groups on patient sex and severity of AUD. We propose a superiority design, whereby MBRP will be superior to referral to online mutual support.

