### Outcomes

#### Overview

All outcomes are assessed at each time point (baseline and at follow-up months: 6, 12, 18, 24, 30, and 36) and are studied over time with change from baseline to the last follow-up period as the analysis metric.

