#### Primary Outcome

Given the focus of the interventions on continuing care for AUD, recovery from AUD was chosen as the primary outcome and is based on the most recent empirical definition of recovery developed by NIAAA [17]. This empirical definition of recovery is a binary (yes or no) outcome defined by achieving all three of the following: (1) remission from *DSM-5* AUD based on an 11-item AUD symptom checklist [66] (endorsing <2 criteria is AUD remission, excepting the craving criterion which may persist even during total abstinence); (2) cessation of heavy drinking (defined as not engaging in heavy drinking over the past 28 days with heavy drinking defined as 4 or more standard drinks per occasion for females, and 5 or more standard drinks per occasion for males, measured by the Timeline Followback [67]); and (3) improvements in functioning and well-being as measured by higher score (from baseline) on the World Health Organization (WHO) Quality of Life [68] domain scores (each of 26 items scored from 1 to 5 on a response scale, which are then transformed linearly to a 0‐100 scale) and the 36-item Short Form Health Survey (SF-36) [69] Mental Health Component Score (scored on a 0‐100 scale). Recovery is defined by the achievement of remission, cessation of heavy drinking, and improvements in functioning and well-being. The assessment of recovery is completed at all time points, with proportion change from baseline to the final follow-up period (3 years postbaseline) assessed as the primary outcome.

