### Statistical Methods

#### Primary Outcome Analysis

We use a generalized linear mixed model (GLMM) that can accommodate a binary outcome (recovery vs not recovery as defined by the NIAAA definition [17]) and random effects that correct for the nonindependence of repeated measures in longitudinal data to assess within-person change over time. The recovery binary variable is created using the 3 indicators included in the definition at each time point. AUD remission is based on not endorsing criteria for AUD (other than craving which may persist even during abstinence), cessation of heavy drinking is defined by no self-reported heavy drinking days, and improvements in functioning and well-being as measured by higher score (from baseline) on the WHOQOL-BREF [68] domain scores (each of 26 items scored from 1 to 5 on a response scale, which are then transformed linearly to a 0‐100 scale) and the 36-item Short Form Health Survey [69] Mental Health Component Score (scored on a 0‐100 scale). The analyses consist of estimating a GLMM with fixed effects of baseline sociodemographics and covariates used in randomization (sex and AUD severity), fixed effects of random assignment to MBRP versus online mutual support referral, and random effects of time.

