#### Interim and Subgroup Analyses

No interim analyses are conducted. As the literature suggests possible differences in outcomes based on sex, gender, race, and ethnicity [112-114], we examine sex, gender, race, and ethnicity as moderators of group effects. We also examine whether there are facilitator effects (eg, effects of a particular MBRP facilitator) by incorporating the facilitator as a random effect in the mixed effects models. We also test whether addiction cycle domains moderate the association between MBRP and primary and secondary outcomes.

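### As listed, the primary model tests one treatment effect common to all visits, whereas the stated primary outcome is the change in recovery from baseline to 3 years

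*Protocol article*

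**What the plan says.** Under Outcomes (Overview), outcomes are measured at baseline and at six follow-up visits from month 6 to month 36, and they "are studied over time with change from baseline to the last follow-up period as the analysis metric". Primary Outcome repeats this for recovery, "with proportion change from baseline to the final follow-up period (3 years postbaseline) assessed as the primary outcome".

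Under Primary Outcome Analysis, recovery is scored repeatedly: "The recovery binary variable is created using the 3 indicators included in the definition at each time point". The analysis is then described as a generalized linear mixed model with fixed effects of baseline sociodemographics, sex and AUD severity, followed by "fixed effects of random assignment to MBRP versus online mutual support referral, and random effects of time". Secondary Outcome Analyses gives the same list of terms. No section names an arm-by-time term or a contrast at month 36.

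Two other statements bear on the point. Objectives hypothesises that MBRP "will be associated with greater odds of recovery from AUD up to 3 years following a drinking change attempt". Trial Design states the aim: "We propose a superiority design, whereby MBRP will be superior to referral to online mutual support".

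**The concern.** The outcome sections point to one time point, the end of year 3. The listed model has one treatment coefficient that pools every visit. These are different questions whenever the effect changes over time. That is a live possibility here: MBRP attendance is open-ended over 36 months, and groups stop if interest falls below two members.

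The trial's single superiority claim depends on which question is tested. A benefit in the first 18 months that had gone by year 3 could be reported as success on a 3-year outcome. A benefit that built up slowly could be missed.

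**Working it through.** **Step 1: what the stated outcome requires.** Recovery includes a higher functioning score than at baseline, so nobody can count as recovered at baseline. The change in proportion from baseline to month 36 is then the month-36 proportion, and comparing the arms on it is a month-36 contrast.

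**Step 2: what the listed model gives.** For participant i at visit t:

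logit P(recovered) = β0 + covariates + θ·arm + u0i + u1i·t

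The arm log odds ratio is θ at every t. Adding a fixed visit effect γt leaves it at θ. Only an arm-by-visit term gives a separate θ36. If the true effect varies, θ is roughly a weighted average over the visits.

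**Step 3: the plan's own power figure.** Sample Size Considerations gives Cohen h = 0.36 (a difference at one time point, 12 months after treatment), two-sided α = 0.05, 215 per group, and power above 0.90. Using power = Φ(h·√(n/2) − 1.96):

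- 0.36 × √107.5 = 3.73
- 3.73 − 1.96 = 1.77
- Φ(1.77) = 0.962

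The statement is correct, but it describes a single-time-point comparison and not the pooled coefficient.

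**Step 4: how far the two tests can differ.** Trials were simulated with 215 per arm, the six follow-up visits and complete data, 200 trials per scenario. Assumptions not in the documents:

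- flat recovery of 20%, 30% or 40% in the referral arm
- a participant random intercept with SD 1.8 on the logit scale
- the shape of the effect over time
- baseline covariates left out

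Effect shapes, as h at months 6, 12, 18, 24, 30, 36:

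- fading: 0.36, 0.36, 0.36, 0.24, 0.12, 0
- late: 0, 0, 0, 0.12, 0.24, 0.36
- constant: 0.36 throughout
- none: 0 throughout

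With 30% in the referral arm, h = 0.36 means 47.4% in the MBRP arm. Three analyses were compared: the listed model (arm, random intercept and random time slope, no fixed time), the same with fixed categorical visit but no interaction, and a month-36 two-proportion test. Entries are the share of trials declaring MBRP superior at two-sided 5%, so the nominal rate under no effect is 2.5%.

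| Effect | Referral recovery | Listed model | Plus fixed visit | Month-36 contrast |
|---|---|---|---|---|
| Fading | 20% | 87% | 97.5% | 1.5% |
| Fading | 30% | 87% | 93.5% | 3% |
| Fading | 40% | 87% | 93.5% | 2.5% |
| Late | 20% | 33% | 60.5% | 95% |
| Late | 30% | 31.5% | 58% | 95.5% |
| Late | 40% | 40% | 53% | 96% |
| Constant | 30% | 99.5% | 100% | 95.5% |
| None | 30% | 3% | 3% | 3% |

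The Monte Carlo standard error at 87% is √(0.87 × 0.13 / 200) = 0.024, or about 2.4 points.

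**The case against.** The strongest reply is that this is a condensed article. A full protocol (version 3.0) exists and may code time and name the contrast. Mentioning random effects of time is often shorthand for a growth model that also fits the mean trend. That much stands: the text shows that a fixed time effect is not listed, not that it is excluded. A reader might infer that the model forces the average trend to zero, but the documents do not support that.

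The reply does not remove the point. The article says what the analyses consist of, and that list does not deliver the outcome stated two sections earlier. Reading in a fixed time trend does not help either, because the arm coefficient stays common to all visits. In the fading scenario the superiority claims rose to between 93.5% and 97.5%.

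A second reply is that the hypothesis in Objectives covers the period up to 3 years, so a whole-period effect may be what is meant. This is fair. It means that month 36 is not the only admissible target, but also that the article supports two different primary tests.

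A third reply is that no section predicts fading. With a constant effect on the log-odds scale, the listed coefficient also describes month 36 and is the more powerful test. This also stands, and it limits the harm to effects that change over time.

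**Conclusion.** The point holds. The primary outcome wording and the primary model, as listed, do not match, and the same applies to the secondary outcomes. Under the assumed shapes the mismatch is large in both directions: about 87% superiority claims with no month-36 difference, and 32% to 40% detection of a late effect that a month-36 contrast finds in 95% to 96%. These figures illustrate and do not forecast. They rest on the assumed shapes, within-person correlation, referral rates and complete data, though the direction was the same at all three referral rates.

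Three stronger inferences are not supported:

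- **That the test is invalid in general.** With no effect at any visit, the listed model favoured MBRP in 3% of trials, close to the nominal 2.5%.
- **That baseline enters as a row of structural zeros.** No section says that baseline recovery is a response in the model.
- **That clustering by MBRP group is ignored.** Interim and Subgroup Analyses plans to examine facilitator effects by "incorporating the facilitator as a random effect in the mixed effects models". Any figure for the consequence would need a group size and an intraclass correlation that the article does not give, and a one-facilitator-per-participant formula does not fit rolling, often cofacilitated groups.

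**What to change.** Choose one target and align the sections before data are unblinded.

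- **If month 36 is intended:** fit the post-baseline visits with fixed visit, arm and arm-by-visit terms and a participant random effect. Keep sex and AUD severity as covariates. Name the month-36 arm contrast as the single primary test, with the average over visits as supportive. Use the same structure for the secondary outcomes.
- **If the whole-period effect in Objectives is intended:** restate the metric in the Outcomes overview and in Primary Outcome as an average over follow-up, and say that this average is the primary contrast.

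Either change is wording only. Recruitment began on September 13, 2023, so no month-36 visit falls due before September 2026.

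The cost of the month-36 option is power when the effect is constant: about 95.5% against 99.5% for the pooled coefficient at h = 0.36 with 215 per arm and complete data. Attrition lowers it further. At the 80% retention aim, 0.8 × 215 = 172 per arm, and Φ(0.36 × √86 − 1.96) = 0.916 as a completers-only approximation, still above the planned 0.90.

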#### Secondary Outcome Analyses

We use a GLMM that can accommodate binary secondary outcomes (achieving at least a 1-level reduction and achieving at least a 2-level reduction in WHO risk levels) and a general linear mixed model that can accommodate continuous secondary outcome measures. In all analyses, we include random effects that correct for the nonindependence of repeated measures in longitudinal data to assess within-person change in secondary outcomes over time. The analyses consist of estimating a mixed model with fixed effects of baseline sociodemographics and covariates used in randomization (sex and AUD severity), fixed effects of random assignment to MBRP versus online mutual support referral, and random effects of time.

#### Mechanisms of Change Analyses

We use GLMM and GLM to examine associations between addiction cycle domains and the primary and secondary outcomes. We hypothesize improvements in executive functioning, self-efficacy, and recovery capital, and reductions in incentive salience and negative emotionality over time predict a higher likelihood of recovery and greater improvement in secondary outcomes at the 3-year follow-up. To test whether MBRP versus online mutual support uniquely impacts mechanisms of behavior change, we use latent growth mediation analyses with randomized condition (independent variable), addiction cycle domains, and self-efficacy over time (mediators), and the recovery outcome or secondary outcomes, as we have done in prior work [109,110]. The product of coefficients approach is used to assess the statistical significance with bootstrapping to obtain 95% CIs of the mediated effects [111]. Sensitivity analyses will also be conducted to estimate the robustness of the mediating effects to the no-omitted confounder assumption [56]. All models are reestimated with the number of sessions of MBRP or online mutual support groups attended as the independent variable.

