### Interventions

#### Overview

MBRP has been tested in randomized clinical trials as a “stand-alone” treatment (without prior treatment) [61], as a primary treatment following detoxification and stabilization [45], as a “rolling group” component of residential treatment [62], and as an “aftercare” intervention following community treatment as usual [44,46]. This study is the first randomized trial of MBRP compared to referral to mutual support in the community and the first trial of MBRP as a continuing care intervention whereby individuals can attend as many sessions as they want (ie, “rolling group”). MBRP is especially well-suited for adaptation from a discrete treatment episode to continuing care, given its emphasis on establishing and maintaining a mindfulness practice that can flexibly be applied in any situation. This contrasts with other evidence-based treatments that emphasize teaching clients to use learned skills for specific high-risk situations (eg, cognitive behavioral therapy–based relapse prevention plans).

Given the focus on MBRP as a continuing care intervention, it was important to select a comparator that reflected existing continuing care models. Continuing care for AUD is largely based on referral to mutual support groups; therefore, referral to mutual support groups was selected as the comparator [63]. We chose a 2-group design and did not randomize to different kinds of mutual support (eg, SMART Recovery vs AA), such that client participants received referral to multiple mutual support options and were informed that they were welcome to select and try out any that interested them (eg, SMART Recovery and AA). Thus, this study assesses the effectiveness of MBRP as continuing care as compared with the typical approach of referring individuals to mutual help, regardless of which mutual help groups participants attend.

Interventions are not modified or discontinued by the research team for any reason, although trial participants could opt to discontinue attending the intervention conditions at any time. No concomitant care or additional interventions are prohibited during the trial.

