#### MBRP Condition

In addition to the elements described above, the orientation session for the MBRP condition includes a review of the Zoom environment, an opportunity to learn Zoom for group sessions (eg, applying virtual backgrounds, breakout rooms, video and mute functions, swapping speaker, and panel view); an overview of MBRP; and an introduction to a free, MBRP mobile app created specifically for this study.

MBRP is delivered by trained facilitators and uses an existing rolling group treatment manual that has demonstrated effectiveness [62] and has been used feasibly via Zoom since March 2020. Participant worksheets and home practices were adapted from the closed-format MBRP manual [49] and guided meditations were drawn from the PracticeMBRP and MindfulRP websites. The rolling group manual consists of 8 sessions of 60 minutes each, covering the content described in Table 1.

Each session begins with a brief mindfulness practice and a discussion of mindfulness concepts (eg, “what is mindfulness?”) and the role mindfulness may play in recovery. The discussion encourages participants to apply the practices learned in the groups to their ongoing recovery. Consistent with a continuing care model, participants can attend as many MBRP sessions as they want to, and for as long as they want. Although the session content repeats every 8 weeks, we have found in our implementation of the program in community settings that individuals continue to attend beyond the full 8 sessions. Although themes are repeated, participants bring new experiences to the session, decreasing the risk of mere repetition. The group composition also includes people in various stages of recovery and familiarity with the material, which can make for richer discussions among group members themselves.

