#### Referral to Online Mutual Support Condition

The orientation session for the referral group is the only intervention provided to the comparator group, consisting of an orientation to online mutual support programs: InTheRooms, AA online, and SMART Recovery. Referral sources for individuals who are in crisis (eg, calling 988) are offered, as well as information about optional mobile apps for those wanting mobile app support (eg, apps to track drinking).

Mutual support groups are free, peer-led organizations designed to help individuals with substance use disorders and other addiction-related problems. Mutual support groups often focus on communication and exchange of addiction and recovery experience and skills. Through shared activities and discussions, participants provide mutual support and learning among individuals facing similar challenges.

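### The session-count re-estimation puts one shared count in place of randomized arm, so its coefficient mixes two unlike session types and loses the protection of randomization; it can support only exploratory associations

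*Protocol article*

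**What the plan says.** The Mechanisms of Change Analyses section sets its aim in these words: "To test whether MBRP versus online mutual support uniquely impacts mechanisms of behavior change". For this it specifies latent growth mediation models in which randomized condition is the independent variable, the addiction cycle domains and self-efficacy are the mediators, and recovery or a secondary outcome is the endpoint. Mediated effects are tested as products of coefficients with bootstrap intervals. One safeguard against confounding is named: "Sensitivity analyses will also be conducted to estimate the robustness of the mediating effects to the no-omitted confounder assumption". The section then closes with: "All models are reestimated with the number of sessions of MBRP or online mutual support groups attended as the independent variable".

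Other sections describe what a session is and who chooses it:

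- **MBRP Condition:** sessions follow an eight-session manual, last 60 minutes and are run by trained facilitators. Attendance is unlimited: "participants can attend as many MBRP sessions as they want to, and for as long as they want".
- **Referral to Online Mutual Support Condition:** "The orientation session for the referral group is the only intervention provided to the comparator group". Any mutual-support sessions are free, peer-led community meetings of whatever kind the participant picks.
- **Interventions, Overview:** "No concomitant care or additional interventions are prohibited during the trial". Participants in either arm may therefore attend mutual-support meetings.
- **Table 2 and Outcomes, Overview:** attendance runs from month 0 to month 36. Outcomes are measured at baseline and every 6 months over the same period.
- **Trial Design:** a superiority design, so the two conditions are expected to differ.

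**The concern.** The closing sentence names one number as the independent variable, in the place that randomized condition held. Three things follow.

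- **Shared slope.** The coefficient assumes that one MBRP session and one mutual-support meeting do the same thing. It also contains no comparison of MBRP with referral, although that comparison is the aim of the section.
- **Unprotected exposure.** Randomization makes arm independent of motivation. It does not do so for attendance. The named sensitivity analysis concerns the mediating effects, which is the assumption left open when arm is the exposure. It does not cover confounding of attendance with the mediator or with the outcome, which arises once attendance replaces arm.
- **Ordering.** Attendance and the repeated measurements overlap for three years. Unless earlier sessions are separated from later ones, people who are already doing well can raise their own session count.

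At stake is how a mechanism result is read. A positive session coefficient, or a mediated effect built on it, is easily taken as evidence that more MBRP works through these domains. It could arise without any MBRP effect, and a real MBRP effect could be hidden.

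**Working it through.** **Inputs.** From the article: 432 participants completed orientation (Results); the power statement uses 215 per group, Cohen h = 0.36 and two-sided alpha .05 (Sample Size Considerations). Session means, their spread, recovery rates and motivation strengths are not in the article. All are assumptions here.

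**1. The plan's own figure.** No figure is stated for the session models. The stated primary power is reproduced: Φ(0.36 × √(215/2) − 1.96) = Φ(1.77) = 0.96, consistent with the claim of more than .90. Nothing below changes it.

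**2. Dilution from a shared slope.** Let arms be equal in size (p = 0.5), with mean sessions m1 (MBRP) and m0 (mutual support), session variances V1 and V0, and true slopes b1 and b0 on the log-odds scale. In a linear approximation the shared slope is

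b = [p·V1·b1 + (1−p)·V0·b0 + p(1−p)(m1−m0)(b1·m1 − b0·m0)] / [p·V1 + (1−p)·V0 + p(1−p)(m1−m0)²].

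Assume gamma-Poisson counts with shape 1, so V = m + m². Take b1 = 0.10 and b0 = 0.

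- m1 = m0 = 5: V = 30 in both arms. b = (0.5 × 30 × 0.10)/30 = 0.05.
- m1 = 5, m0 = 20: V1 = 30, V0 = 420. Numerator: 1.5 + 0.25 × (−15) × 0.5 = 1.5 − 1.875 = −0.375. Denominator: 15 + 210 + 56.25 = 281.25. b ≈ −0.001.

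A logistic simulation (300 runs) gave the same answers: 0.052 and −0.001. Arm-specific terms in the same runs gave 0.102 to 0.103.

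**3. Sign when sessions do nothing.** Suppose arm has a real effect (log-odds 0.72, odds ratio about 2) and session counts have none. Only the between-arm part of the numerator remains, 0.25 × (m1 − m0) × 0.72, so the sign follows relative attendance. Simulation (432 participants, 1000 runs, standardized log(1 + sessions)):

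| Mean sessions, MBRP / mutual support | Count significant | Median odds ratio per SD |
|---|---|---|
| 8 / 8 | 4% | 1.00 |
| 8 / 40 | 55%, all in the direction of harm | 0.82 |
| 8 / 3 | 29%, all in the direction of benefit | 1.14 |

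**4. Motivation alone.** Here neither arm nor sessions affects anything. Unmeasured motivation raises both attendance and recovery. Nominal level 5%, 1000 runs per cell.

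| Assumption set | Weak | Moderate | Strong |
|---|---|---|---|
| A: mean 5 sessions, 30% recovery; motivation adds 0.7 to log attendance and 0.3, 0.5 or 0.8 log-odds to recovery, per SD | 27% | 57% | 90% |
| B: mean 10 sessions; motivation adds 0.4, 0.6 or 0.8 to log attendance and 0.2, 0.4 or 0.6 log-odds to recovery, per SD | 10% | 37% | 86% |
| B, path from sessions to mediator (correlation of motivation with mediator 0.2, 0.3, 0.4) | 23% | 77% | 99% |

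Without confounding, set B gave 4%. The randomized-arm test stayed at 4% to 6% throughout.

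**5. Ordering.** If the mediator level drives attendance (0.4 on log attendance per SD) and sessions do nothing, the path from sessions to mediator was significant in essentially 100% of runs. The recovery term stayed near 5%, because the mediator was given no effect on recovery in that set-up.

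**6. What better modelling cures.** Separate terms repair step 2. They do not repair step 4. In set A with arm and two session terms, the MBRP term was still falsely significant in about 17%, 32% and 65% of null runs. In set B, adding arm to the shared count left 9%, 38% and 81%. With a true MBRP slope of 0.10 plus motivation confounding, the arm-specific slope averaged 0.13, 0.14 and 0.16.

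**The case against.** The strongest reply is that this is a re-estimation added after the model that answers the stated aim. The arm-based mediation model and the primary and secondary models all keep random assignment, and the article claims no causal effect of attendance. That stands, and it limits the point to a supplementary analysis.

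Second, the sentence does not say that sessions are summed. It may mean each participant's count for the assigned condition, as in the per-protocol rule under Analysis Approach and Missing Data, which asks for two MBRP sessions or, correspondingly, two mutual-help sessions. This stands in part. If it means separate terms or within-arm models, the shared-slope problem goes. If it means one variable holding each person's own-condition count, steps 2 and 3 still apply, because the simulations were built in just that way.

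Third, the counting window, any lag and the handling of people who attend both kinds of group are details that an article may leave to the full protocol or analysis plan. That is fair. A reader might infer that the plan fixes a 36-month total; the article does not say so, and the silence is not itself the fault. The exposure, however, is stated, and it is self-selected under every reading.

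Fourth, the percentages come from single-time-point regressions on assumed inputs, not from the latent growth models. They show direction and possible size, not an expected error rate.

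**Conclusion.** The point holds as a limit on one supplementary analysis. As worded, the re-estimated models replace a randomized exposure with a self-selected count and, on the plain reading, give two unlike session types one slope. That slope can be halved, vanish or change sign with relative attendance alone. Motivation can make it significant well above 5% when no session has any effect. The pooling part depends on reading the sentence as one variable across arms; the loss of randomization does not. All sizes rest on assumed attendance and motivation.

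Two stronger readings are not supported. A reader might infer that the trial's main result, its arm-based mediation test or its sample size is compromised; each keeps randomized condition or is computed without attendance. A reader might also infer that separate session terms would yield a valid MBRP dose effect; step 6 shows that they do not when motivation is unmeasured.

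**What to change.** In the re-estimated models:

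- keep randomized arm;
- enter MBRP sessions and mutual-support sessions as separate terms, or fit within-arm models;
- count only sessions attended before the mediator or outcome being modelled, using the existing 6-monthly assessments;
- adjust for baseline covariates, as the primary and secondary models already do;
- extend the omitted-confounder sensitivity analysis to attendance as an exposure.

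State that the results are non-randomized, exploratory associations and are not to be read as an MBRP dose effect. The first three steps address pooling and ordering. Stable motivation confounding is left over, which is why the label is needed.

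The cost is wording and some programming. The Confidentiality section says that treatment attendance is recorded, and Table 3 lists a mutual-help activity measure every 6 months, so new data collection appears unnecessary. The downside is less precision for each session term. Follow-up is still under way, so the change can be made before analysis.
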